### Outcome measures

#### Primary outcomes

##### Safety

The number of falls and adverse events will be recorded. Participants in the CON, UNSUP, and UNSUP + groups will record their falls and adverse events during and outside exercise sessions with a diary [39, 40]. In the SUP and SUP + groups, the sports scientist will register the incidence of falls and adverse events during exercise sessions, and participants will register them outside the exercise sessions using a diary.

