**Methods:**

Participants (*n* = 120, aged 60–75 years) will be randomly allocated into five groups: 1-Control (CON), 2-Supervised exercise without motivational intervention (SUP), 3- Supervised exercise with motivational intervention (SUP +), 4- Unsupervised exercise without motivational intervention (UNSUP) and 5- Unsupervised exercise with motivational intervention (UNSUP +). Over 24 weeks, all exercise groups will participate in a multicomponent exercise program three times/week (performed in group classes at a center for SUP and SUP + , or home without supervision but with the help of a mobile app for UNSUP and UNSUP +), while the CON group will maintain their usual lifestyle. The motivational intervention (for SUP + and UNSUP + groups) will be based on the self-determination theory, including strategies such as phone calls, interactive workshops, motivational messages, informative infographics and videos. Primary outcomes will include safety, adherence, costs, and lower-body muscular function using a leg press machine. Secondary outcomes will include upper-body muscular function, physical and cardiorespiratory function, blood pressure and heart rate, body composition, health-related quality of life, cognitive performance, anxiety, depression, physical activity levels, sleep and sedentarism, biochemical markers, motivators and barriers to exercise. Assessments will be conducted at baseline, mid-intervention (*i.e.,* week 13), at the end of the intervention (*i.e.,* week 25), and 24 weeks later (*i.e.,* week 49).

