One of the factors that could moderate the effectiveness of exercise programs is adherence. In this regard, a recent meta-analysis by our research group showed that adherence to unsupervised exercise programs is usually low [29], probably due to a lack of motivation. Applying motivational strategies might help increase adherence to exercise programs, which could eventually result in greater training-induced adaptations [30–32]. Some studies have analyzed the impact of motivational strategies during exercise programs in older adults [33, 34]. However, these studies analyzed the influence of motivational strategies in supervised or unsupervised exercise interventions separately, but never before have they been examined in a single study.

The Promoting Training Programs for Health (PRO-Training) trial aims to cover all the abovementioned research gaps. The main goal of this RCT will be to determine the impact of supervision and motivational strategies on the safety, adherence, efficacy, and cost-effectiveness of different exercise programs for improving physical and mental health in older people.

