### Statistical analysis

Data will be preferentially presented as mean ± standard deviation or as proportions for continuous and categorical variables, respectively. Data normality will be assessed by the Kolmogorov–Smirnov test and will be log-transformed in case of non-normal distribution. Baseline differences will be assessed through a one-way ANOVA. A two-way mixed ANCOVA (group [*i.e.*, CON, SUP, SUP + , UNSUP, and UNSUP +] x time [*i.e.,* baseline, mid, post-intervention, and follow-up assessments]) will be performed, adjusting for baseline values as well as for any other sociodemographic/descriptive variables that may differ between groups (*e.g.,* age, sex). Subsequent post-hoc tests will be conducted to determine which groups significantly differ. Effect sizes will be calculated to assess the magnitude of the differences [87]. Falls and fall-related injuries will be presented as rates/person (ITT analysis) and rates/person/year (± 30 days; PP analysis), and as numbers. Adverse events and dropouts will be compared between groups through Chi-squared tests. Differences in adherence rates will be analyzed using an ANOVA test. Correlation analyses will be used to assess associations between motivators, barriers, and adherence to exercise sessions. Whenever possible, statistical analyses will be performed on an intention-to-treat (ITT) basis (including all randomized participants). The potential effects of missing values and dropouts will also be explored using multiple imputation and sensitivity analyses [88]. As recommended, a complementary per protocol (PP) analysis will be performed (*i.e.,* including only those participants with valid data for baseline and post-intervention assessments and an adherence to exercise program of at least 80%) [89]. SPSS version 24.0 (IBM Corp., Armonk, NY) will be used for statistical analysis, and the significance level will be set at p ≤ 0.05 for all tests.

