## Discussion

The main objective of the present trial is to examine the role of supervision and motivational strategies on the safety, adherence, efficacy, and cost-effectiveness of 4 different exercise programs for improving physical and mental health among people between 60 and 75 years old. We hypothesize that all exercise programs will be safe, and those that add cognitive-behavioral and motivational strategies will result in greater adherence and efficacy. Furthermore, we expect that UNSUP + will be the most cost-effective option, thereby increasing the accessibility of exercise to all older adults and consequently improving their health and quality of life.

As recommended by the World Health Organization, older adults should perform 150–300 min/week of moderate-intensity aerobic physical activity, 75–150 min/week of vigorous-intensity aerobic physical activity, or a combination thereof, as well as multicomponent physical activity focusing on functional balance and resistance training (≥ 3 days per week) [90]. The benefits of multicomponent exercise for mental and physical health are widely known [91–94]. Regular exercise helps in the prevention and management of different chronic diseases (*e.g.*, diabetes, obesity or overweight, hypertension, osteoporosis, or osteopenia) [95–98], thus leading to reduced attendance to medical consultations. According to Santos et al. [99], the global cost of inaction on physical inactivity would cost healthcare systems approximately 47.6 billion $ per year. If we add to this the low participation of older adults in physical activity, which decreases with age, we justify the need for safe and effective exercise programs for this population [16, 100].

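### In-session falls and adverse events are logged by staff in the supervised arms but by participant diary in the unsupervised arms, so the supervised-versus-unsupervised safety comparison is partly confounded with who records

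*Protocol article*

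**What the plan says.** The Safety section of the protocol article sets two recording rules.

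- **CON, UNSUP, UNSUP+:** "Participants in the CON, UNSUP, and UNSUP + groups will record their falls and adverse events during and outside exercise sessions with a diary".
- **SUP, SUP+:** "In the SUP and SUP + groups, the sports scientist will register the incidence of falls and adverse events during exercise sessions"; for everything else, "participants will register them outside the exercise sessions using a diary".

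The Abstract places safety among the primary outcomes: "Primary outcomes will include safety, adherence, costs, and lower-body muscular function using a leg press machine". The Background gives the main goal as "to determine the impact of supervision and motivational strategies on the safety, adherence, efficacy, and cost-effectiveness of different exercise programs".

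Under Statistical analysis, "Adverse events and dropouts will be compared between groups through Chi-squared tests". Falls and fall-related injuries are to be presented as rates and numbers, and no between-arm test is named for them. The section separates neither outcome by setting (in or out of session) or by source (staff or diary).

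**The concern.** The question is whether supervision changes the safety of exercise. For events during exercise, supervision also determines who writes the event down: a professional who is present at the session, or a participant alone at home. A difference in recorded in-session events between the supervised and unsupervised arms can then come from true risk, from completeness of recording, or from both, and these data cannot separate them.

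The Background makes wider use of unsupervised programs conditional on their safety being confirmed. If minor events at home go unrecorded, supervised exercise can look less safe than it is relative to home exercise, or a real excess at home can be hidden.

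The blinding arrangements do not cover this. Outcome assessors are blinded, but in-session events are recorded by the sports scientist running the session or by the participant. According to Randomization and blinding, neither can be blinded.

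**Working it through.** The article states no event rate, capture rate or power for safety, so there is no figure to reproduce. The check has two parts.

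**1. Which comparisons are affected (from Safety and Trial groups)**

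| Arm | In-session recorder | Out-of-session recorder |
|---|---|---|
| SUP, SUP+ | sports scientist | diary |
| UNSUP, UNSUP+ | diary | diary |
| CON | no trial sessions | diary |

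- Supervised versus unsupervised, in-session: the recorder differs, so this comparison is confounded.
- Supervised versus unsupervised, out-of-session: the method is the same.
- SUP versus SUP+, and UNSUP versus UNSUP+: the method is the same within each pair.

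Exposure to the difference is up to 3 sessions × 24 weeks = 72 sessions per participant.

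**2. Possible size (all capture rates and risks are assumptions)**

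Let *cs* be staff capture, *cd* diary capture (taken as equal in all arms and settings), and *s* the share of true events that occur in sessions. Let true risk be equal in both groups.

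- In-session only: apparent ratio = *cs*/*cd*.
- All events: apparent ratio of expected recorded events = [*s*·*cs* + (1 − *s*)·*cd*]/*cd* = 1 + *s*(*cs*/*cd* − 1).

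With *cs* = 0.95 and *cd* = 0.60:

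- *s* = 1: 0.95/0.60 = 1.58
- *s* = 0.5: (0.475 + 0.300)/0.60 = 0.775/0.60 = 1.29
- *s* = 0.25: (0.2375 + 0.450)/0.60 = 0.6875/0.60 = 1.15

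Range over diary capture, with *cs* = 0.95:

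| Diary capture | In-session only | Half in-session | A quarter in-session |
|---|---|---|---|
| 90% | 1.06 | 1.03 | 1.01 |
| 70% | 1.36 | 1.18 | 1.09 |
| 60% | 1.58 | 1.29 | 1.15 |
| 50% | 1.90 | 1.45 | 1.23 |

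The ratio exceeds 1 only while *cs* > *cd*. If staff recorded less completely than the diaries, it would fall below 1.

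In participants: equal allocation, which the article does not state, gives 120/5 = 24 per arm and 48 per pooled pair. At an assumed in-session risk of 20%, the expected numbers with a recorded event are 48 × 0.20 × 0.95 = 9.1 supervised and 48 × 0.20 × 0.60 = 5.8 unsupervised.

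Chance of a falsely significant supervised excess, for in-session events only, at 48 versus 48, two-sided 0.05 and 20% true risk: with 95% staff capture it is about 3%, 10% and 24% for diary capture of 90%, 70% and 50%. The nominal chance in that direction is 2.5%. This pooled two-group contrast is an illustration; the plan compares groups, of which there are five.

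**The case against.** Several points on the other side stand.

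- **Scope.** A reader might infer that the whole primary safety comparison is confounded. It is not: only in-session events in the supervised-versus-unsupervised contrast are affected. CON follows no exercise program, so it has no in-session events to miss.
- **Size.** The 1.58 assumes that every counted event is in-session. The planned adverse-event test has no such restriction, and pooling dilutes the ratio as shown. Even undiluted, 9 versus 6 of 48 gives p of about 0.4, so a spurious significant result is far from assured.
- **Direction.** One might infer that the error favours the trial's hypothesis. The Discussion says "We hypothesize that all exercise programs will be safe", and fuller capture in SUP and SUP+ works against that for those two arms. An unblinded sports scientist with up to eight participants could also under-record.
- **Analysis.** One might read the chi-squared test as assuming equal capture. The article is silent on this, and a split by setting may sit in a plan that is not shown.
- **Remedy.** A shared diary does not guarantee equal capture, since supervised participants may skip what they know staff have logged or be prompted by staff. Relying on diaries alone would also drop witnessed harms from the comparison.

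Some asymmetry is unavoidable, because no staff attend home sessions. That does not remove the point. The recording rule is stated and tied to the randomised factor, and an analysis split cannot recover in-session diary data that supervised participants were never asked to provide.

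**Conclusion.** The point holds for in-session falls and adverse events in the supervised-versus-unsupervised contrast. There, the effect of supervision cannot be separated from the effect of who records. More recorded events in the supervised arms is the probable direction, but it is not certain.

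The size cannot be computed from the article. The figures of 1.58 (in-session alone), 1.29 (half in-session) and 1.15 (a quarter in-session) rest on assumed capture of 95% and 60%, equal true risk, and equal diary capture across arms for out-of-session events. With good diaries (90%) the distortion is 1.06 at most.

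The plan should be changed, because a primary outcome is affected and the remedy is cheap.

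**What to change.** 1. Ask SUP and SUP+ participants still in the intervention to enter in-session events, as well as out-of-session events, in the diary they already keep. The sports scientist's log continues.
2. Make the comparison of diary-reported events the like-for-like analysis across groups. Beside it, give the all-source comparison that includes the staff log, so that no observed harm is dropped.
3. Report in-session and out-of-session events separately, and state the source of each.
4. For participants who have already finished, treat the out-of-session comparison as the only like-for-like one, and say that it does not answer the in-session question.

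**Cost.** One diary instruction and a few lines of analysis text. It can reach only those still training: the Trial status section dates the first recruitment to 7 September 2022 and expects recruitment to finish in late 2024, so the number is below the 48 or so supervised participants implied by equal allocation. The like-for-like comparison uses a less complete source, and the supervised arms will contain two recording regimes, before and after the change. The date of the change should be recorded and reported.

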##### Adherence to the program

Adherence to the program will be calculated as a ratio between the sessions completed from those initially prescribed ([sessions completed/total sessions expected] × 100), where 0% indicates total non-adherence and 100% indicates full adherence [40]. The sports scientist will record adherence to the exercise program in the SUP and SUP + groups [41], while in the UNSUP and UNSUP + groups, it will be automatically registered through the mobile app [42].

##### Costs

Total costs and costs per participant will be calculated for each intervention group. The mean difference in quality-adjusted life-year (QALY) scores at the end of the intervention will be assessed to analyze the cost-utility. QALY scores range from 1 (perfect health) to 0 (dead) [43]. Furthermore, an incremental cost-effectiveness ratio (ICER) will be calculated by dividing the adjusted cost differences by the effect differences. Data on health-related quality of life measured through the EuroQoL five dimensions (EQ-5D) questionnaire will be used for the calculations [44–47].

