### Study design

The study will follow a single-blind randomized, parallel design. Participants will be randomized into 5 groups (Fig. 2): 1- Control group (CON), 2- Supervised exercise without motivational intervention (SUP), 3- Supervised exercise with motivational intervention (SUP +), 4- Unsupervised exercise without motivational intervention (UNSUP) and 5- Unsupervised exercise with motivational intervention (UNSUP +). Assessments will be conducted at baseline (week 0), mid-intervention (week 13), at the end of the intervention period (week 25), and 24 weeks later (week 49).

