### Trial groups

All participants allocated to exercise intervention groups will complete a 24-week multicomponent exercise program consisting mostly of resistance exercises (3 sessions per week; 60 min per session). The exercise program will be reported following the Consensus on Exercise Reporting Template (CERT) [38] (see Supplementary Table 2). After completing the baseline assessment, participants will be randomly allocated to the 5 study groups. After randomization and irrespective of intervention group allocation, a member research team member will inform the participant about the intervention and assessment plan.

The exercise program for all intervention groups will be divided into 3 difficulty levels, increasing every 8 weeks. Each will include 3 sessions comprising of warm-up, balance, resistance, aerobic, and flexibility exercises (Tables 1 and 2). Further information about the training variables is available in Supplementary Table 3.

**Table 1 Tab1:** Supervised exercise program

	**Session nº**	**Exercise nº**	**Intensity report**	**LEVEL 1**	**LEVEL 2**	**LEVEL 3**	**Type**
WARM-UP	1, 2 & 3	1	-	Seated ankle circumduction			Joint mobility
		2	-	Knee flexo-extension			
		3	-	Hip circumduction			
		4	-	Forward–backward shoulder circumduction			
		5	-	Wrist circumduction			
		6	-	Neck mobility			
		7	-	Diagonal foot touches	Foot touches forward, to the side and back with hands on the waist	Foot touches forward, to the side and back with arms in cross position	Balance
		8	-	Heel lifts	One leg balance	One leg balance with arms in cross position	
		9	-	Lateral movement without impact	Lateral movement with impact	Rope skipping	Soft cardio
		10	-	´V´ front	Knee-elbow	Low skipping	
MAIN ACTIVITY	1	1	-	One leg balance with arms in cross position	One leg balance with leg abduction	One leg balance with shoulder flexion	Balance
		2	RIR	Machine chest press	Cable crossover	Dumbbell chest press	UB push (pectoral, triceps)
		3	RIR	Box squat	Goblet squat	Jump squat	LB (quadriceps, gluteus)
		4	RIR	Pulley shoulder flys	Alternating dumbbells shoulder flys	Simultaneous dumbbells shoulder flys	UB pull (trapezius, deltoid)
		5	RIR	Assisted TRX lunge	Lunge	Weighted lunge	LB (quadriceps, gluteus)
		6	RPE	Front plank with shoulder touches	Front plank with knees	Front plank	Core
		7	RIR	Seated rowing machine	Standing cable row (medium height)	Unilateral dumbbell row	UB pull (dorsal)
		8	RIR	Knee-banded seated hip abduction	Monster walk	Clamshell	LB (gluteus)

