### Data collection and management

Outcomes will be assessed at baseline, mid-intervention (*i.e.,* week 13), at the end of the intervention (*i.e.,* week 25), and 24 weeks later (*i.e.,* week 49). At each measurement point –except for the mid-intervention measurement, which will only involve 1 session– participants must perform all assessments in 5 different days interspersed by at least 48 h and a maximum of 1 week. Trained assessors will conduct all assessments. A detailed scheme of the outcomes assessed in this study is shown in Figs. 1 and 3.

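### The cost-utility outcome is described as a 0-to-1 score at a single visit, which is a utility weight and not a QALY

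*Protocol article*

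**What the plan says.** Costs are listed among the primary outcomes. The Costs section bases cost-utility on a comparison at one time point: "The mean difference in quality-adjusted life-year (QALY) scores at the end of the intervention will be assessed to analyze the cost-utility". The next sentence fixes the scale: "QALY scores range from 1 (perfect health) to 0 (dead"). It continues that "an incremental cost-effectiveness ratio (ICER) will be calculated by dividing the adjusted cost differences by the effect differences", and closes with the data source: "Data on health-related quality of life measured through the EuroQoL five dimensions (EQ-5D) questionnaire will be used for the calculations".

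The time frame comes from other sections. Under Trial groups, "All participants allocated to exercise intervention groups will complete a 24-week multicomponent exercise program". Study design places the assessments at weeks 0, 13, 25 and 49, with week 25 as the end-of-intervention visit. Data collection and management describes the week 13 visit as reduced ("except for the mid-intervention measurement, which will only involve 1 session"). The text does not show whether the EQ-5D is among the measures taken then, and the assessment figures are not available here.

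The Discussion states the expected result: "we expect that UNSUP + will be the most cost-effective option".

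**The concern.** A quantity anchored at 0 for dead and 1 for perfect health, and read at a single visit, is a utility weight. It has no time unit. A QALY is that weight accumulated over time, that is, the area under the utility curve in years. The Costs section calls the first quantity by the name of the second and mentions no time weighting.

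If the plan is carried out as worded, the primary cost-utility result would be a difference in utility points. Used as the denominator of a cost-utility ratio, it would give cost per utility point. That figure cannot be compared with cost-per-QALY figures from elsewhere, which matters for a trial that hopes to inform public policy.

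**Working it through.** The article gives no QALY, utility difference, cost or ICER figure, so there is nothing to reproduce. Two checks are possible.

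**Check 1: can the stated range apply to QALYs at the end of the intervention?**

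Inputs: 24-week programme (Trial groups); end visit at week 25 and follow-up at week 49 (Study design); maximum score 1 (Costs). The most a participant can accrue is 1 × weeks/52:

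- to week 24: 24/52 = 0.46
- to week 25: 25/52 = 0.48
- to week 49: 49/52 = 0.94

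A score that can reach 1 at the end of the intervention is therefore not QALYs accrued to that point. It is a utility.

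**Check 2: how far apart are the two quantities?**

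Let d be the between-arm utility difference at week 25, with equal baselines. The QALY difference is the trapezoidal area under the utility-difference curve:

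ΔQALY = Σ ½(dᵢ + dᵢ₊₁) × (tᵢ₊₁ − tᵢ)/52

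The overstatement factor is d/ΔQALY. The path of the difference over time and the horizon are assumptions; the article gives neither.

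| Horizon | Assumed path of the difference | ΔQALY | Factor |
|---|---|---|---|
| Week 25 | immediate and sustained | 25/52 = 0.481d | 2.08 |
| Week 25 | linear to full at week 13, then kept | (6.5 + 12)/52 = 0.356d | 2.81 |
| Week 25 | linear from week 0 to week 25 | 12.5/52 = 0.240d | 4.16 |
| Week 25 | none until week 13, then linear | 6/52 = 0.115d | 8.67 |
| Week 49 | immediate and kept | 49/52 = 0.942d | 1.06 |
| Week 49 | immediate, fading to 0 between weeks 25 and 49 | (25 + 12)/52 = 0.712d | 1.41 |
| Week 49 | linear to week 25, then kept | (12.5 + 24)/52 = 0.702d | 1.42 |
| Week 49 | linear to week 25, then fading to 0 at week 49 | (12.5 + 12)/52 = 0.471d | 2.12 |

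With 24 weeks in place of 25, the immediate and linear factors are 52/24 = 2.17 and 52/12 = 4.33.

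**Effect on an ICER** (illustration with an assumed cost difference of 300 euros and d = 0.03):

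- d taken as QALYs: 300/0.03 = 10,000
- immediate and sustained to week 25: 300/(0.03 × 25/52) = 20,800 per QALY
- linear build-up to week 25: 300/(0.03 × 12.5/52) = 41,600 per QALY

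**The case against.** The strongest reply is that this is a condensed article and the wording is merely loose. The section says EQ-5D data will feed calculations and cites sources for them, so an area-under-the-curve derivation may sit in the full protocol or a health-economic plan. Scores at the end of the intervention could mean QALYs accrued up to then. This stands in part: a reader might infer that the raw EQ-5D score will certainly be entered as the QALY, and the text never says that outright. But the point does not rest on an omission. The article states a range and a time point, and Check 1 shows that the two together cannot describe accrued QALYs.

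Four further inferences are tempting, and the document does not support them:

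- **That the ICER will be reported as cost per QALY with this score underneath.** The ICER sentence refers only to effect differences, and no cost window is given. The inference is natural, because no other effect is named in the section, but it remains conditional.
- **That the overstatement is 2- to 4-fold as a matter of fact.** That range belongs to a 25-week horizon and two assumed paths. The alternatives in the table run from about 1.1 to 8.7.
- **That baseline utility is ignored.** The Statistical analysis section plans a general ANCOVA adjusted for baseline values. It does not say that this covers the cost-utility comparison, so stating it is worthwhile, but the adjustment is not absent from the plan.
- **That every programme would look more cost-effective than it is.** This holds only for a positive utility gain at added cost. A factor common to all arms leaves the sign and ordering of ICERs against a shared comparator unchanged, so the comparative expectation about UNSUP + could survive. It need not survive if the arms follow different paths: with the same d at week 25, an immediate effect yields twice the QALYs of a linear one (0.481d against 0.240d).

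**Conclusion.** The concern holds in a conditional form. The definition is wrong as written: a 0-to-1 score compared at one visit is a utility, and at most about 0.46 to 0.48 QALY can accrue over the 24 to 25 weeks of the intervention period. That part needs no assumption beyond the document's own schedule and scale.

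The numerical consequence does rest on assumptions: the difference is used untransformed as the QALY gain and ICER denominator, the horizon is 25 weeks, baselines are equal and the gain is positive. The gain is then overstated about 2.1-fold for an immediate, sustained effect and about 4.2-fold for linear build-up, and a positive ICER is understated by the same factor. Because this concerns a primary outcome, it should be settled before analysis.

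**What to change.** - Compute each participant's QALYs as the trapezoidal area under EQ-5D utility from week 0 to week 25, using week 13 as well if the EQ-5D is collected at that visit.
- Estimate between-arm QALY differences adjusted for baseline utility, and state that the baseline adjustment in the Statistical analysis section applies to this comparison.
- Name QALYs as the ICER denominator, and count costs over the same window.
- Reword the 0-to-1 sentence so that it describes EQ-5D utility and not QALYs.

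The cost is a change of wording and a few lines of analysis on data already being collected. The downside is that the resulting ICERs will look less favourable than ratios built on the end-of-intervention utility difference.

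### The cost-utility analysis calls a 0-to-1 EQ-5D utility at week 25 a QALY score; read literally, this overstates 25-week QALY gains about 2.1- to 4.2-fold

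*Protocol article*

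**What the plan says.** The Costs paragraph under Primary outcomes in the protocol article sets out the economic analysis.

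- Effect measure: "The mean difference in quality-adjusted life-year (QALY) scores at the end of the intervention will be assessed to analyze the cost-utility".
- Its scale: "QALY scores range from 1 (perfect health) to 0 (dead".
- The ratio: "an incremental cost-effectiveness ratio (ICER) will be calculated by dividing the adjusted cost differences by the effect differences".
- The data source: "Data on health-related quality of life measured through the EuroQoL five dimensions (EQ-5D) questionnaire will be used for the calculations".

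The timing comes from other sections. Study design places the later assessments "at the end of the intervention period (week 25), and 24 weeks later (week 49". Trial groups says that exercise participants "will complete a 24-week multicomponent exercise program". The article mentions no weighting by time, no area under a utility curve and no horizon for the QALYs.

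**The concern.** The scale and the single time point describe a utility weight, not a QALY. A QALY is the utility multiplied by the years lived at that utility. If the week-25 difference in utility is entered in the ICER as it stands, the effect is counted as though it had lasted a full year, while programme costs build up over 24 weeks. The fault does not depend on imbalance at baseline: with perfectly balanced arms the stated quantity would still not be a QALY.

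This matters because costs are one of four primary outcomes, cost-effectiveness is part of the main aim, and the Discussion expects the unsupervised programme with motivation to be the most cost-effective option. The Abstract also looks ahead to public policy. A ratio with a utility difference in the denominator cannot be reported as cost per QALY or compared with cost-per-QALY results from elsewhere.

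**Working it through.** **Inputs from the article.** QALY score range 0 to 1 (Costs). End of intervention at week 25 and last follow-up at week 49 (Study design). Programme of 24 weeks (Trial groups).

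**Assumptions.** The article gives neither the size nor the time course of the EQ-5D difference. Let the between-arm utility difference be 0 at baseline and d at week 25, never above d in between. A year is 52 weeks. The factors below do not depend on the size of d.

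**Step 1: the stated range.** The most that can accrue is perfect health throughout, T/52.

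- Week 25: 25/52 = 0.48
- Week 49: 49/52 = 0.94

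A value of 1 cannot be reached at either point, so the stated range does not reproduce as QALYs accrued in this trial. It fits a utility.

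**Step 2: QALYs gained by week 25.** QALY difference = area under the difference curve, in years. Overstatement factor = d / area.

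| Path to week 25 | Area | Factor |
|---|---|---|
| Full effect from the start | 25/52 = 0.481d | 2.08 |
| Linear to week 13, then held | (0.5×13 + 12)/52 = 0.356d | 2.81 |
| Linear to week 25 | 0.5×25/52 = 0.240d | 4.16 |

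With a year of 52.18 weeks the two ends become 2.09 and 4.17.

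**Step 3: effect on the ICER.** With an unchanged cost difference, the ratio is understated by the same factor. Illustration with assumed figures, 300 euros extra cost and d = 0.03:

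- Point score: 300/0.03 = 10,000
- Immediate effect: 300/(0.03×0.481) = about 20,800 per QALY
- Linear build-up: 300/(0.03×0.240) = about 41,600 per QALY

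**Step 4: ranking.** Suppose two programmes reach the same d at week 25, one linearly (0.240d) and one by week 13 and then held (0.356d). The point score treats them as equal. In QALYs the second yields 18.5/12.5 = 1.48 times the first. If its extra cost over control is between 1 and 1.48 times that of the first, the point score favours the first programme and cost per QALY favours the second. If the paths have the same shape in all arms, one factor rescales every ratio and the ranking stays as it is.

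**Step 5: outside the assumptions.** If the week-13 difference is m times d, the area is (12.5m + 6)d/52. For m = 2 this is 31d/52 = 0.596d, a factor of 1.68. The factor reaches 1 only at m = 46/12.5 = 3.68.

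**The case against.** The strongest reply is that this is a short article summary. It says EQ-5D data enter calculations that are cited to other sources, and a score at the end of the intervention could loosely mean QALYs accrued by then. The trapezoid rule, value set and horizon are commonly left to a fuller plan. Part of this stands: a reader might infer that the analysis will certainly omit time weighting, and the article does not establish that. It does establish that the definition it prints is wrong, because the 0-to-1 range is incompatible with QALYs accrued over 25 weeks and no other section corrects it.

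A reader might also quote a range of about 1.4- to 4.2-fold. That mixes two horizons. The 1.4 needs a linear gain held to week 49, (0.5×25 + 24)/52 = 0.702d, a horizon that the cost-utility sentence does not name. Nor is it a lower bound: a gain reached by week 13 and held to week 49 gives (0.5×13 + 36)/52 = 0.817d, a factor of 1.22, and an immediate gain held to week 49 gives 0.942d, a factor of 1.06. A longer horizon may also change the cost difference, so the ICER need not move by the same factor.

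Finally, the article names no cost-per-QALY threshold and its hypothesis is relative. A changed ranking needs utility paths that differ between arms. That is possible here, but not shown.

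**Conclusion.** The point holds as an error in a stated definition for a primary outcome. The quantity described is a week-25 utility, not a QALY. Taken literally at the horizon the article names, it overstates QALYs gained, and understates cost per QALY for a given cost difference, by about 2.1-fold (immediate full effect) to 4.2-fold (linear build-up). These factors rest on equal baselines and a difference that never exceeds its week-25 value; they are not figures that the article fixes. Distortion of the programme ranking is a possibility that depends on unequal paths. The sample size and the safety, adherence and muscle-function outcomes are not affected.

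**What to change.** - Call the week-25 EQ-5D value a utility and delete the definition of a QALY score running from 0 to 1.
- Compute each participant's QALYs as the trapezoidal area under the EQ-5D utility curve from week 0 to week 25. Use week 13 only if EQ-5D is collected there: Data collection and management limits that visit to one session, and the readable text does not show its content. Baseline and week 25 are enough for a trapezoid.
- Divide the cost difference over weeks 0 to 25 by the between-arm QALY difference over the same weeks.
- Add a week-49 horizon only if costs from week 25 to week 49 are also collected. The Costs paragraph does not say that they are.

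For the week-25 horizon this is a change of wording and analysis made before the data are analysed, with no new data collection. The downside is that reported QALY gains will be smaller and the ICERs less favourable. If a fuller plan already uses the area under the curve, the published text should be reconciled with it.
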